## Abstract

**Background:**

Youth in the child welfare system (child welfare–involved [CWI] youth) have high documented rates of mental health symptoms and experience significant disparities in mental health care services access and engagement. Adolescence is a developmental stage that confers increased likelihood of experiencing mental health symptoms and the emergence of disorders that can persist into adulthood. Despite a high documented need for evidence-based mental health services for CWI youth, coordination between child welfare and mental health service systems to increase access to care remains inadequate, and engagement in mental health services is low. Navigator models developed in the health care field to address challenges of service access, fragmentation, and continuity that affect the quality of care provide a promising approach to increase linkage to, and engagement in, mental health services for CWI youth. However, at present, there is no empirically supported mental health navigator model to address the unique and complex mental health needs of CWI youth and their families.

**Objective:**

Using a randomized controlled trial, this study aims to develop and test a foster care family navigator (FCFN) model to improve mental health service outcomes for CWI adolescents (aged 12-17 years).

**Methods:**

The navigator model leverages an in-person navigator and use of adjunctive digital health technology to engage with, and improve, care coordination, tracking, and monitoring of mental health service needs for CWI youth and families. In total, 80 caregiver-youth dyads will be randomized to receive either the FCFN intervention or standard of care (clinical case management services): 40 (50%) to FCFN and 40 (50%) to control. Qualitative exit interviews will inform the feasibility and acceptability of the services received during the 6-month period. The primary trial outcomes are mental health treatment initiation and engagement. Other pre- and postservice outcomes, such as proportion screened and time to screening, will also be evaluated. We hypothesize that youth receiving the FCFN intervention will have higher rates of mental health treatment initiation and engagement than youth receiving standard of care.

**Results:**

We propose enrollment of 80 dyads by March 2024, final data collection by September 2024, and the publication of main findings in March 2025. After final data analysis and writing of the results, the resulting manuscripts will be submitted to journals for dissemination.

**Conclusions:**

This study will be the first to produce empirically driven conclusions and recommendations for implementing a family mental health navigation model for CWI youth with long-standing and unaddressed disparities in behavioral health services access. The study findings have potential to have large-scale trial applicability and be feasible and acceptable for eventual system implementation and adoption.

**Trial Registration:**

ClinicalTrials.gov NCT04506437; https://www.clinicaltrials.gov/study/NCT04506437

**International Registered Report Identifier (IRRID):**

DERR1-10.2196/49999

## Introduction

### Background

After a decade-long decline in the number of youth in placement outside of the home (ie, foster care) in the United States, the foster care caseload in most states rose between 2014 and 2019. The current foster care caseload exceeds 400,000 in the United States [1], with another approximately 165,000 youth receiving court-mandated services within their own homes [2]. Youth in out-of-home or foster care placement and those remaining in the home but are child welfare system and court involved are collectively referred to as *child welfare–involved (CWI)* and are considered some of the most underserved with respect to behavioral health care access in the United States. The COVID-19 pandemic has further increased the number of youth entering the child welfare system owing to having lost parents or caregivers from COVID-19–related death [3].

Rates of mental health symptoms and diagnoses in CWI youth are high, particularly among adolescents. The vast majority are referred to child welfare agencies because of child abuse or neglect [4], and, as a result of trauma experienced in their home of origin, the majority display mental health or behavioral health challenges [5]. According to the National Survey of Child and Adolescent Well-Being, much more than half of a national sample of youth in out-of-home care display behavioral or social competency problems [6], and studies that include smaller samples or regional samples suggest similar results [7,8]. Among 815 CWI youths aged 12 to 17 years, 43% reported at least 1 mental health concern, including attention-deficit/hyperactivity disorder (ADHD; 19%), suicidality (14%), anxiety (14%), depression (9%), and co-occurring substance use (23%) [9]. Youth in out-of-home care report higher rates of mental health problems than peers of a similar age [10,11]. Depending on the study, between 35% and 85% of all youth in out-of-home care experience a mental health condition [12], and youth in out-of-home care are 3 times more likely to be prescribed psychotropic medications for their mental health conditions [13].

Adolescence is a critical developmental period for the assessment, diagnosis, and treatment of mental health symptoms. Vulnerability to mental health disorders increases significantly in adolescence, and the emergence of disorders during this period (eg, early psychosis) increases the likelihood of persistence into adulthood [14]. Rates of depression escalate in adolescence, particularly among girls with extensive trauma histories (such as CWI youth) who are at substantially higher risk for poor mental health, substance use, and legal outcomes. Adolescence also encompasses unique factors associated with the transition to young adulthood (eg, for those aged 16-17 years), making it a highly vulnerable developmental stage for CWI youth [9]. Adolescents who are placed in out-of-home care face unique risks because chronic placement instability is the norm rather than the exception, particularly for older adolescents [15-17]. Studies demonstrate that youth with mental health difficulties are more likely to be moved from one placement to another, and these moves create or exacerbate mental health concerns [18,19]. These concerns are exacerbated for racial and ethnic minoritized youth [20] and reify ongoing and long-standing behavioral health disparities among CWI youth. Identifying adolescent mental health needs, matching these needs to appropriate services, and providing supports for mental health care access and linkage have great potential to resolve or offset challenges manifesting in adulthood.

Despite high need for evidence-based mental health services for CWI youth, ample evidence suggests that coordination between child welfare and mental health service systems is inadequate. Access to care for CWI youth is hampered by multiple system-level barriers, such as frequent change of placement as well as underreporting of mental health problems by foster parents, social workers, and physicians [13]. National survey data (n=3803) highlight a substantial gap between the identified need for and use of mental health services in child welfare populations, particularly among older youth: 66% of those aged 11 to 14 years have clinically significant mental health needs, yet only 26% use mental health services [21]. Data local to the site of the proposed project demonstrate critical gaps in mental health screening and full assessment, with only 28% of all youth assessed within 2 months of case opening, 45% by 3 months, and 69% by 6 months. Furthermore, by 12 months, 11% of youth had their case closed before ever receiving a mental health assessment [22].

The public health impact of gaps in mental health services delivery among CWI youth is significant. Untreated mental health concerns among CWI youth persist when they leave the out-of-home care system and transition to independence [23]. CWI youth are also likely to have dual (or *crossover*) involvement with the juvenile legal system [24], which can further exacerbate unmet services needs and disparities within this population. Persistent mental health concerns in this population can also contribute to placement instability [25] and re-entry into the child welfare and juvenile legal systems [26], which both compound mental health difficulties and strain public health systems and economies. Unaddressed mental health services needs also perpetuate racial and ethnic disparities in services access, engagement, and quality in this population, as well as perpetuate the root causes of these disparities (eg, systemic racism and discrimination), which have notable public health consequences. Data local to the site of the proposed project mirror national statistics, documenting the alarming overrepresentation of African American and Latinx youth in the child welfare system [21]: 36% of CWI youth aged 12 to 17 years are African American compared with 6.1% of the entire county population.

Navigator models (ie, the use of a navigator to support access to, and transition through, complex health care systems) provide a promising approach to increasing linkage to, and engagement in, mental health services for CWI youth with high rates of unaddressed mental health concerns. Navigator models have been successfully developed and deployed in other contexts (eg, cancer and HIV), with demonstrated improvements in service tailoring, linkage, and treatment retention [27]. A small number have also been developed for general adolescent populations with behavioral health needs (eg, the Family Navigation Project) [28]. However, existing mental health navigator models have not been empirically developed or tailored for system-involved (ie, child welfare or juvenile legal system) youth and families who have unique, complex multisystemic factors associated with mental health care needs and access.

Mobile health (mHealth) technology is gaining empirical support for improving adolescent mental health and behavioral health (eg, substance use) outcomes. Data suggest that SMS text messaging is a useful tool to improve youth attendance in outpatient mental health treatment [29] and can prevent adolescent substance use relapse [30]. A recent meta-analysis (n=14 studies) concluded that SMS text messaging technology is a promising substance use prevention strategy for adolescents and young adults [31], the majority of whom have access to, and regularly use, their mobile phones despite unique adolescent barriers to constant access and use (eg, service payment, continuous service, and no access while at school during the day). Our own work with community-supervised court-involved adolescents and their caregivers suggests that families and involved juvenile legal personnel and providers all heavily rely on digital and mHealth technology for communication and care coordination (eg, SMS text messaging, emailing, and social media instant messaging) [32].

Despite the promise and prevalence of mHealth technology, there is no systematic, empirically supported strategy leveraging mHealth to enhance family-based approaches to improving CWI youth mental health service use and outcomes. Studies show that only some caregivers are ready for electronic messaging support for health care [33] and that depending on caregiver race or ethnicity (eg, Latinx ethnicity), socioeconomic status (eg, low status) and age (eg, younger age), SMS text messaging may be more or less appealing as a tool for adolescent health care engagement [33,34]. Parent outreach via bidirectional SMS text messaging to enhance the uptake of adolescent vaccine and well care services improved these adolescent health outcomes [35], suggesting that a caregiver-level mHealth intervention may be effective in improving other adolescent health outcomes (eg, mental health). Caregivers of CWI youth have the additional context of juvenile legal system and child welfare system surveillance and involvement (eg, mandated youth treatment, sanctions-based approach to noncompliance, and information-sharing concerns) that might differentially affect their response to mental health navigator interventions, particularly those that incorporate mHealth for service tracking or monitoring. Given the high numbers of staff, providers, and systems that often operate separately and with minimal coordination to support CWI youth, mHealth has unique potential to improve communication between families and systems to support linkage to, and engagement in, mental health services.

Given the significant need for an empirically driven, timely, coordinated, and collaborative interagency response to addressing the mental health needs of CWI youth, the proposed project aims to develop and test an empirically derived navigator intervention that relies on interagency codevelopment and incorporates state-of-the-art mHealth technology to improve linkage to, and engagement in, mental health services among CWI youth. A randomized clinical trial (N=80 caregiver-youth dyads) comparing the navigator intervention with standard of care (clinical case management services) for CWI youth has the potential to have large-scale trial applicability and to be feasible and acceptable for eventual system implementation and adoption.

### Study Objectives

This study will be the first to develop and test a foster care family navigator (FCFN) intervention for CWI youth that has the potential to significantly improve adolescent mental health disparities, particularly for racial and ethnic minoritized youth. The primary goal of the study is to assess the feasibility, acceptability, and preliminary impact of the FCFN intervention on the mental health services cascade of care (eg, screening, assessment, and treatment initiation) outcomes. Using a randomized controlled trial (RCT) design, we will randomize 80 families to receive either the FCFN intervention or standard of care (clinical case management services): 40 (50%) to FCFN and 40 (50%) to control. Qualitative exit interviews will inform the feasibility and acceptability of the services received during the 6-month period. Primary trial outcomes are mental health treatment initiation and engagement. Other pre- and postservice outcomes, such as proportion screened and time to screening, will also be evaluated.

### Juvenile Justice Behavioral Health Services Cascade

The juvenile justice behavioral health services cascade, hereinafter referred to as the *cascade*, was recently developed (adapted from the HIV cascade of care models) [36] as part of the Juvenile Justice Translational Research on Interventions for Adolescents in the Legal System (JJ-TRIALS) study, a National Institute on Drug Abuse–funded, large-scale, multisite research and implementation science collaborative. JJ-TRIALS developed the *cascade* as a unifying framework for juvenile legal system and behavioral health partners to collectively (1) identify system-level substance use service strengths and needs along the continuum of care and (2) codevelop and test interventions to improve adolescent substance use service linkage and outcomes along the *cascade*. The *cascade* framework can also inform multiple interrelated research goals and be easily adapted for empirical application and testing with other youth populations (eg, foster care youth), systems (eg, child welfare system) and health (eg, mental health) outcomes [37] as in the proposed study. Figure 1 presents a hypothetical adapted *cascade* framework for CWI adolescent populations using the same cascade of care steps but modifying the involved systems (eg, from juvenile legal system to child welfare system). Table 1 presents step definitions (developed by the JJ-TRIALS group) adapted to CWI youth and system processes.

**Figure 1 figure1:**
[figure not shown]
Example of juvenile justice behavioral health services cascade adapted for child welfare–involved (CWI) youth.

**Table 1 table1:** Behavioral health services cascade definitions adapted for child welfare–involved youth and the foster care mental health (FCMH) system.

Step	Operational definition	Calculated proportion (based on step)
A. Child welfare referrals	Total number of referrals to FCMH over a designated period of time, less any youth already in treatment at that time	N/A^a^
B. Screened	Subset of FCMH referrals (A) with a screening date	B/A
C. Full clinical assessment	Subset of FCMH referrals (A) with a full clinical assessment (includes if follow-up to screening or other clinical assessment)	C/A
D. In need	Subset of FCMH referrals (A) with a need for mental health treatment based on screener, clinical assessment, or other sources of information	D/A
E. Referrals to treatment	Subset of those in need (D), referred by the child welfare or FCMH systems to mental health treatment	E/D
F. In treatment	Subset of those referred to treatment (E) who have a treatment start date	F/E
G. Engaged in care	Subset of those in treatment (F) who stay in treatment for at least 6 weeks (based on treatment discharge minus treatment start date)	G/F
H. Continuing care	Subset of those engaged in treatment (G) who are still receiving treatment after 90 days	H/G

^a^N/A: not applicable.

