#### Randomization

Participants will be randomized (using a computer-generated randomization tool) to either the FCFN intervention group (40/80, 50%) or the standard of care group (40/80, 50%) directly after consent and completion of the baseline assessment.

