**Transition (percentage of those identified as in need; EMR)**
Percentage referred for treatment and percentage who initiated treatmentTime to referral and initiation (number of days)

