**Retention (percentage of those referred for treatment; EMR)**
Engaged in care (≥6 weeks of attendance)Continuing care (number of total sessions completed)

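### Treatment initiation and engagement each carry two conflicting denominators, none of them all randomised youth, and the article does not say which one the arm comparison uses

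*Protocol article*

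**What the plan says.** Study Objectives: "Primary trial outcomes are mental health treatment initiation and engagement". The Hypotheses section expects both to be higher with the navigator than with standard of care.

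The article then gives each outcome a denominator in two places.

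- **Table 1 (cascade definitions).** Referral, step E, is "Subset of those in need (D), referred by the child welfare or FCMH systems to mental health treatment". Initiation, step F, is "Subset of those referred to treatment (E) who have a treatment start date", calculated as F/E. Engagement, step G, is "Subset of those in treatment (F) who stay in treatment for at least 6 weeks", calculated as G/F.
- **Textbox 1 (study measures).** Initiation is listed under "Transition (percentage of those identified as in need; EMR", which is F/D in the letters of Table 1. Engagement, worded "Engaged in care (≥6 weeks of attendance", is listed under "Retention (percentage of those referred for treatment; EMR", which is G/E.

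Two further sections bear on the comparison but name no denominator. Primary Outcome Measures (Cascade of Care Services) lists the percentage initiating and, for each youth, whether he or she engaged. Statistical Analysis (Cascade Outcomes) fits a generalized linear mixed model (GLMM) to dichotomous outcomes with arm as a fixed effect.

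Randomisation takes place "directly after consent and completion of the baseline assessment".

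**The concern.** The two sources disagree for both primary outcomes, so the article does not fix one estimand for either.

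The choice also matters for validity. Randomisation protects a comparison of everyone allocated. It does not protect a comparison of youth who later reached a step that the arm may influence. Suppose the navigator brings more hesitant youth to referral or to a first session. The navigator arm's referred or started subset is then less selected than the control arm's, and the conditional percentage can fall while more of the randomised youth start or stay. The hypothesis concerns youth by arm, and a denominator of all randomised youth answers it directly.

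Two candidate denominators per outcome also leave room to choose after results are known. The trial is meant to give a preliminary estimate of impact for a larger trial, so a wrong sign here would carry forward.

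**Working it through.** **1. Figures in the article.** No event rates or expected differences are given for these outcomes, so there is no planned figure to reproduce. The allocation adds up: 40 + 40 = 80.

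**2. The definitions side by side.** A = all randomised in the arm (for this calculation), D = in need, E = referred, F = started, G = engaged.

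| Outcome | Table 1 | Textbox 1 | Primary Outcome Measures | GLMM text |
|---|---|---|---|---|
| Initiation | F/E | F/D | base not stated | analysis set not stated |
| Engagement | G/F | G/E | base not stated | analysis set not stated |

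This gives four ratios on three denominators (D, E, F), two per outcome. A is not among them.

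**3. When each denominator is formed.**

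- *Need (D).* Recruitment is around the clinic contact, for example the screening visit, so need may be known before randomisation for some youth and after it for others.
- *Referral (E).* In the control arm, making the referral is the case managers' task under the allocated care. The percentage referred is itself listed as an outcome. For youth not yet referred at baseline, E is formed after allocation.
- *Start (F).* This is a primary outcome. If the initiation hypothesis is true, the set used as denominator of G/F differs between arms for that very reason.

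**4. Illustration. All counts are assumed.**

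Control: A 40, D 32, E 20, F 14, G 10. Navigator: A 40, D 32, E 30, F 19, G 12.

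| Ratio | Control | Navigator | Difference (points) |
|---|---|---|---|
| Initiation F/E | 14/20 = 70.0% | 19/30 = 63.3% | -6.7 |
| Initiation F/D | 14/32 = 43.8% | 19/32 = 59.4% | +15.6 |
| Initiation F/A | 14/40 = 35.0% | 19/40 = 47.5% | +12.5 |
| Engagement G/F | 10/14 = 71.4% | 12/19 = 63.2% | -8.3 |
| Engagement G/E | 10/20 = 50.0% | 12/30 = 40.0% | -10.0 |
| Engagement G/A | 10/40 = 25.0% | 12/40 = 30.0% | +5.0 |

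On the same data, the two stated denominators for initiation give opposite signs. Both stated denominators for engagement favour control, although more navigator youth engage.

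**5. How general this is.** Assume 50% of youth are referred in either arm and start with probability 0.70 in both. The navigator adds a further proportion x who are referred and start with probability s.

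- Difference in F/E = (0.5 × 0.7 + x·s)/(0.5 + x) - 0.7 = x(s - 0.7)/(0.5 + x)
- Difference over all randomised = x·s

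| s | F/E difference, x = 0.1 to 0.4 | All-randomised difference, x = 0.1 to 0.4 |
|---|---|---|
| 0.2 | -8.3 to -22.2 | +2.0 to +8.0 |
| 0.5 | -3.3 to -8.9 | +5.0 to +20.0 |
| 0.7 | 0 | +7.0 to +28.0 |

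In this model the sign reverses whenever the added youth start at a rate above 0 but below that of youth referred anyway.

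**6. The same for G/F.** Assume 35% start in either arm and engage with probability 0.70, and the navigator adds starters y who engage with probability g. Then G/F = (0.35 × 0.7 + y·g)/(0.35 + y). For y = 0.1 to 0.2 and g = 0.3 to 0.5, G/F is 55.5% to 65.6% against 70.0% in control. Engaged over all randomised is 0.245 + y·g = 27.5% to 34.5% against 24.5%.

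**The case against.** The strongest reply is that Table 1 is not an outcome definition. It stands in the Introduction and adapts step definitions from a juvenile justice framework meant for system-level use. Its step A counts clinic referrals less youth already in treatment, which is not the randomised sample. Textbox 1 likewise begins from a court cohort. The passages on the comparison itself speak of dichotomous outcomes by arm and of whether each youth engaged, with no restriction to those referred or started. A model over all randomised youth, with non-starters coded as no, fits that text, and an analysis set is often left to the full protocol or analysis plan.

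Much of this stands. A reader might infer that the planned comparison is certainly non-randomised, or that it will reverse the true effect. The documents support neither inference: they never say that the GLMM is restricted to a subset, and every count and rate in the reversal calculations is assumed. Nor do they support saying that the navigator changes who is in need; the six sessions do not cover that determination.

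What does not stand is that this is only omitted detail. Textbox 1 is the trial's own list of measures and it also conditions on subsets. It contradicts Table 1 for both primary outcomes, and no section states an all-randomised denominator. The pilot purpose lowers the stakes of any single test but leaves the estimate of preliminary impact needing one definition.

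**Conclusion.** The point holds as a stated contradiction with a possible consequence for validity. Each primary outcome has two incompatible denominators, none is all randomised youth, and the analysis text does not settle the matter.

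If F/E, G/E or G/F were used for the arm comparison, it would not be a randomised comparison, because referral and start can follow allocation and may differ by arm. F/D is less exposed, to the extent that need is determined before randomisation.

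The size cannot be estimated from the documents. In the assumed example the conditional ratios other than F/D run from -6.7 to -10.0 points, while the all-randomised differences are +12.5 (initiation) and +5.0 (engagement). This rests on the navigator adding youth who are less likely to start or stay than those who would have come anyway, without enough gain among the latter to offset it. If the added youth behave like the others (s = 0.7 above), F/E shows no difference while the all-randomised difference is positive. If the GLMM is in fact meant to include everyone, the analysis is sound and only the wording needs correcting.

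**What to change.** Define both primary outcomes as yes or no for every randomised youth, within 6 months of randomisation:

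1. Initiation: has a treatment start date.
2. Engagement: started treatment and stayed engaged for at least 6 weeks.

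Count youth who were not referred or did not start as no. State in the Cascade Outcomes analysis that the GLMM uses this denominator. If a restriction to youth in need is wanted, use only need status documented before randomisation.

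Align Table 1 and Textbox 1. While doing so, settle how the 6 weeks are measured: Table 1 takes discharge date minus start date, whereas Textbox 1 and Primary Outcome Measures refer to attendance. Also say how a start dated before randomisation is counted, since the eligibility criteria do not exclude youth already in treatment.

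Keep F/E, F/D, G/E and G/F as secondary or descriptive cascade figures, with a statement that they are not read as randomised effects.

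The cost is wording only. Cascade data are already to be extracted from medical records in both arms at baseline and at 1, 3 and 6 months. The reported percentages will be lower because the denominator is larger.

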### Assessment Data Collection

Multiple sources of data will be collected, including electronic medical records (EMRs); mobile phone or web entry in the Fostering Connections web application; and self-reports from the FCFNs, youth, and caregivers (Textbox 1). Cascade mental health services–level data will be extracted from EMRs at baseline and at 1, 3, and 6 months for participants in both conditions. Assessments will be conducted via mobile phone or tablet device, depending on participant preference.

Study measures.

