#### Primary Outcome Measures

##### Cascade of Care Services

We will collect EMR data that will include (1) percentage screened (for mental health needs), percentage assessed (received full mental health assessment), and percentage in need (determined to meet medical necessity criteria for mental health services); (2) time to screening, full assessment, and determination of need (number of days); (3) percentage referred for mental health treatment as well as percentage who initiated treatment; (4) time to referral and initiation (number of days); (5) whether the youth engaged in treatment (whether they had ≥6 weeks of treatment attendance); (6) number of total mental health treatment sessions completed; (7) sociodemographics (to provide collateral EMR data on race and ethnicity, sex, education, income, legal history, and placement type); (8) Child and Adolescent Needs and Strengths (CANS) screener and full assessment (the number and descriptions of needs and strengths and based on the Diagnostic and Statistical Manual of Mental Disorders, Fifth Edition [DSM-5], diagnosis per the CANS rating and resources manual with regard to children and youth aged 5-18 years); and (9) Pediatric Symptom Checklist score (collected by the specialty mental health provider and entered into the EMR as part of standard clinical and billing practice).

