## Results

The study was funded by the National Institute of Mental Health on April 20, 2020. The trial is open and recruiting. We propose the enrollment of 80 dyads by March 2024 and final data collection by September 2024. After final data analysis and the writing of the results, the manuscripts will be submitted to appropriate journals for dissemination, with main findings published by March 2025.

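### The primary engagement outcome has two incompatible definitions and two denominators, and its Table 1 form is open to distortion by start timing

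*Protocol article*

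**What the plan says.** The Study Objectives section of the protocol article states: "Primary trial outcomes are mental health treatment initiation and engagement". Engagement is then defined in three places.

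- Table 1, step G (operational definition column): youth who started treatment (step F) and remained for 6 weeks or more, "based on treatment discharge minus treatment start date". The proportion is G/F, so the denominator is youth with a treatment start date.
- Textbox 1, Retention: at least 6 weeks of attendance, as a percentage of those referred for treatment (step E of Table 1).
- Primary Outcome Measures, Cascade of Care Services: "whether the youth engaged in treatment (whether they had ≥6 weeks of treatment attendance"). No denominator is given.

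Step H of Table 1 (continuing care) is nested in step G: "Subset of those engaged in treatment (G) who are still receiving treatment after 90 days".

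On the observation window, the Assessment Data Collection section says that cascade data are "extracted from EMRs at baseline and at 1, 3, and 6 months for participants in both conditions". The Results section leaves 6 months after the end of enrolment: "We propose the enrollment of 80 dyads by March 2024 and final data collection by September 2024".

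**The concern.** The same records can give different primary results depending on which section the analyst follows, in four respects.

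- **Open episodes.** A youth still in care at 6 months has no discharge date, so the Table 1 formula returns nothing for some of the best-engaged youth. Step H shows that the table expects such youth to be in step G, so the table is at odds with itself.
- **Episode time versus attendance.** Discharge minus start measures how long an episode stayed open, not whether the youth attended.
- **Denominator.** Started (Table 1) and referred (Textbox 1) are different groups.
- **Late starts under G/F.** A youth who starts in the last 6 weeks of the window enters the denominator but cannot enter the numerator. Starting treatment happens after randomisation and is what the navigator is meant to change. Conditioning on it lets a difference in start timing appear as a difference in engagement.

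**Working it through.** The article gives no engagement rate, effect size or power figure, so there is no stated figure to reproduce. The check compares the definitions and then does the date arithmetic.

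**1. Three records under the two rules**

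| Record | Table 1 rule | Attendance rule |
|---|---|---|
| Attending regularly for more than 6 weeks, still in care at month 6 | No discharge date, no score | Engaged |
| One visit, episode closed administratively 7 weeks later | Engaged | Not engaged |
| Start after about day 140 | In the denominator, cannot qualify | Cannot qualify |

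**2. Denominators.** Because G is within F and F within E, G/F = (G/E) ÷ (F/E). The two proportions agree only if every referred youth starts. If G/E is equal in the arms but F/E differs, G/F differs.

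**3. Latest qualifying start.** Window length minus 42 days: 182 − 42 = day 140. Windows of 180 to 183 days give day 138 to 141, or month 4.5 to 4.6. I take the 6-month clock to start at randomisation, as the Study Design section does for the questionnaires.

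**4. How many might start too late.** The article gives no treatment-start times. The nearest figures are the local assessment times in the Background: "with only 28% of all youth assessed within 2 months of case opening, 45% by 3 months, and 69% by 6 months". Assume, for illustration, that starts follow this curve, that it is linear between 3 and 6 months, and that case opening coincides with randomisation:

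- By month 4.62 (day 140.6 of a 182.6-day window): 45 + 24 × (4.62 − 3)/3 = 58.0%.
- In the last 6 weeks: 69 − 58.0 = 11.0 points.
- Share of those reached by 6 months: 11.0/69 = 16%. A lag of 0 to 30 days from assessment to start gives 16% to 18%.

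**5. Spurious difference between arms under G/F.** Let r be the true 6-week retention (assumed, equal in both arms) and L the late-start share. Observed G/F = r × (1 − L).

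- r = 70%, L = 5% (FCFN) and 16% (control): 66.5% − 58.8% = +7.7 points.
- r = 70%, L = 25% and 16%: 52.5% − 58.8% = −6.3 points.
- With r = 50% to 90%, the first case ranges from +5.5 to +9.9 points and the second from −4.5 to −8.1.
- With equal L, the difference is zero.

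**6. Open episodes under the literal Table 1 rule.** Let s be the share of retained youth whose episode is still open at 6 months (assumed), with r = 70%. Scored as failures, G/F = r(1 − s). Scored as missing, G/F = r(1 − s)/(1 − rs).

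| s | As failures | As missing |
|---|---|---|
| 20% | 56% | 65% |
| 50% | 35% | 54% |
| 80% | 14% | 32% |

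**The case against.** Table 1 stands in the Introduction and adapts definitions from another research group. The Methods section on primary outcomes uses attendance, which needs no discharge date, and step H shows that open episodes were meant to count. How an open episode is credited at the data cut is often left to an analysis plan. This is a pilot aimed at feasibility, acceptability and preliminary impact.

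Much of that stands. A reader might infer that youth still in care cannot be scored in this trial at all. The documents do not support this: it is true only of the Table 1 parenthesis read literally. A reader might also infer that a 6-month limit on late starters is an error in itself. It is not. Engaged by 6 months among all randomised youth is a legitimate outcome, and a navigator that speeds entry to care should get credit for it. The distortion described here comes from conditioning on having started.

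Nor is 16% a minimum. The Background figures time assessment from case opening for all youth. The trial clock starts after consent and baseline, and petitions may already be open at entry. Time elapsed before randomisation lowers the late-start share, while the lag from assessment to treatment raises it. The net direction is unknown. A similar calculation for the 90 days of step H would not bear on a primary outcome, and Textbox 1 measures continuing care by number of sessions.

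The objection does not remove the conflict. Table 1 calls its entries operational definitions and adapts them to this clinic's system. Two stated rules and two stated denominators for one primary outcome are a contradiction, not an omitted detail.

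**Conclusion.** The point holds as an inconsistency in a primary outcome, with one identifiable route to bias. The article gives two incompatible rules (discharge minus start, attendance) and two denominators (started, referred). The Table 1 rule, read literally, leaves open episodes unscored, conflicts with step H and counts open-episode time as engagement. Under G/F, youth who start after about day 140 count against their arm whatever their retention.

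The date arithmetic is firm to within a day or two. The sizes are not. The 16%, the 70% retention and the late-start and open-episode shares are assumptions or proxies. They show that a gap of several points in either direction is possible, not that one is expected. The documents do not show that the arms will differ in start timing or in open episodes, or which arm would gain.

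**What to change.** 1. In Table 1, step G, replace the discharge-minus-start parenthesis with the attendance rule of Textbox 1 and the Cascade of Care Services section. State what counts as 6 weeks of attendance. A bare span of 42 days from first to last session would still count two isolated visits as engaged.
2. Credit youth still in care with their attendance up to the data cut.
3. Use one denominator throughout, preferably all randomised youth, with the outcome worded as engaged by 6 months. This removes the conditioning on having started, and late starters then properly count as not engaged by that date.
4. If G/F is kept, limit it to youth who start by about day 140, or extend the passive EMR extract by 6 weeks (182 + 42 = day 224).

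Items 1 to 3 are mainly wording changes. The attendance rule needs session dates; the article lists a total session count, so their availability in the EMR should be confirmed. Limiting G/F to early starters loses some youth and still conditions on starting. The extended extract is optional: it needs no participant contact but moves final data collection from September to about mid-November 2024 and may need a minor ethics amendment.
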